## Abstract

**Introduction:**

Sleep-disordered breathing affects 1.6 million people in the UK. The recognised treatment is positive airway pressure (PAP) therapy, delivered via a generic conventional interface (mask). PAP therapy improves morbidity, mortality and quality of life, but treatment effectiveness depends on interface fit and tolerance. Interface side effects include pressure ulcers, skin reactions and interface leak. Three-dimensional (3D) printing is an innovative technology that can produce customised interfaces.

**Aims:**

The primary aim is to assess the impact of customised versus conventional interfaces on residual Apnoea Hypopnea Index at 6 months.

**Methods and analysis:**

This is a randomised control trial via block randomisation, minimised by age >65 and ethnicity, using a computerised random number generator. Patients with sleep-disordered breathing under the care of the Royal Free London NHS Foundation Trust will be recruited. Patients new to therapy will be randomised to customised interface or conventional interface for 6 months. A sample size of 160 is required for 80% power with a significance of 5%, accounting for a 20% dropout rate. Descriptive statistics will report demographics. The primary and secondary outcomes will be compared using linear regression adjusted for baseline score.

**Ethics and dissemination:**

This protocol has been approved by the Hampshire B Research Ethics Committee (REC reference: 22/SC/0405). Results will be disseminated to healthcare professionals and patients through conferences, open-access journals, newsletters, a study webpage, infographics, animations, social media and healthcare awards.

**ISRCTN registration number:**

74082423.

STRENGTHS AND LIMITATIONS OF THIS STUDYThe randomised control trial design enhances the reliability of findings by reducing selection bias.Block randomisation minimised by age and ethnicity ensures a balanced representation of these variables, which are most likely to affect facial geometries across treatment groups.The well-defined target population ensures that results will apply to patients with sleep-disordered breathing.The lack of blinding and the single-site design could introduce bias in assessing outcomes.It has not been possible to include a health economics assessment due to the constraints of funding.

## Introduction

 Sleep-disordered breathing (SDB) is a term encompassing conditions including obstructive sleep apnoea (OSA), complex sleep apnoea and chronic ventilatory failure. Chronic ventilatory failure is commonly caused by chronic obstructive pulmonary disease, obesity-related respiratory failure, neuromuscular disease and chest wall deformity. Symptoms of SDB are multiple and include excessive daytime sleepiness, headaches, impaired cognition, breathlessness, sleep disturbance, nocturia, fatigue, memory loss and reduced libido.^1^ Untreated SDB increases the risk of cardiovascular events and is associated with more frequent healthcare utilisation, including hospital admissions.^1^ Additionally, untreated SDB influences societal factors, such as quality of life (QoL), road traffic accidents and productivity.^1^ A measure of severity in SDB is the Apnoea Hypopnea Index (AHI). Both continuous positive airway pressure (CPAP) and non-invasive ventilation (NIV), collectively referred to as positive airway pressure (PAP), can treat SDB and are crucial to improving patients’ QoL and health-related outcomes. PAP therapy is administered via a tight-fitting mask (interface) attached to the patient’s face. Outcomes such as residual AHI are critical clinical measures of PAP therapy effectiveness for individual patients.

The effectiveness of PAP therapy depends on how well the interface fits the user. Interface leak has been found to cause ineffective ventilation, high residual AHI, persistent nocturnal desaturations and treatment failure.^2^,^4^ Pressure ulcers are also a documented side effect of PAP therapy, which can impact the ability to concord with treatment.^5^

Interfaces are currently limited to conventional interfaces supplied by PAP device manufacturers, which come in limited sizes (small, medium large) and do not consider different facial geometries. Thus, ineffective therapy due to a lack of interface fit is commonly observed. Impaired effectiveness or poor treatment tolerance can reduce QoL, potentially affecting morbidity and mortality and escalating healthcare utilisation.

Three-dimensional (3D) printing is a pioneering technology, which has been used in a range of clinical environments. Several investigators have considered using 3D printing in developing customised interfaces. Case studies^6^,^11^ in paediatric patients demonstrated a significant reduction in interface leak with improved compliance, effectiveness of PAP therapy (reduced residual AHI) and health-related QoL. Hsu *et al*^12^ undertook a feasibility study with 40 participants comparing conventional and customised interfaces. They reported less headgear force was required in the customised group, which resulted in better comfort scores. A small (n=6) crossover study^13^ evaluated the feasibility of 3D-printed customised nasal interfaces and found interface leak comparable between customised and conventional interfaces. Additionally, they reported that the customised interfaces could deliver the required PAP therapy pressures. Similarly, Cheng *et al*^14^ assessed a customised nasal interface developed using 3D printing technology against a conventional cushion and reported a lower residual AHI in the customised interface. However, these studies are limited to a single ethnicity group, in those with OSA alone or very specific patient groups (paediatrics with facial deformities), meaning the results are not generalisable. Furthermore, research to date has only considered short-term outcomes.

This project aims to develop and assess the clinical utility of 3D printing to customise PAP therapy interfaces.

### Research question

What is the clinical impact of customised PAP therapy interfaces versus conventional interfaces in the treatment of patients with SDB?

### Hypothesis

This study hypothesises that customised interfaces will result in greater improvements in residual AHI compared with conventional interfaces, with better PAP concordance due to reduced discomfort and side effects.

### Primary research objective

A randomised controlled trial (RCT) to assess medium-term clinical effectiveness of customised interfaces versus conventional interfaces as assessed by the primary outcome of residual AHI (worse of two nights measured by cardiorespiratory sleep study) at the primary endpoint of 6 months.

### Secondary research objectives

To assess the clinical impact of customised interfaces on interface fit (leak), concordance with PAP therapy and symptoms compared with conventional interfaces.

## Methods and analysis

### Patient and public involvement

Service users were actively involved in the research design; specifically, they provided feedback on the proposed methodologies and dissemination plan and coproduced the lay summary. They reviewed and completed all the intended outcome measures. Participants provided feedback and ideas on reducing the burden of participating in research and codesigned the recruitment strategy. A patient/public advisory group will meet quarterly to provide input into the conduct of the trial.

### Study design

RCT, with patients randomised by block randomisation, minimised by age (<65, ≥65) and ethnicity (Caucasian, Asian and Black), to customised interface or conventional interface, by a computerised random number generator. The primary outcome is residual AHI at the primary end point of 6 months. Based on clinical expertise and published research, ethnicity and age are the biggest factors affecting facial geometry^15 16^ and thus have been included in the stratification.

### Patient entry

Patients will be recruited from those under the care of the sleep and ventilation service at the Royal Free London NHS Foundation Trust (RFL), United Kingdom (UK). The RCT has been designed as a pragmatic trial and is embedded into the existing clinical pathways.

### Inclusion criteria

Diagnosis of sleep discorded breathing: AHI≥15.Patients naive to domiciliary PAP therapy.Age ≥18 years.

### Exclusion criteria

AHI <15.Excessive facial hair which they are unwilling to shave.Age <18 years.Existing facial pressure ulcers.Unable to provide informed consent.Known allergy to silicone.Keloid scarring.Previous domiciliary PAP therapy.

### Withdrawal and stopping criteria

Participants will have the right to withdraw from the study at any time without providing a reason. Any data already collected will remain in the study.

### Data management

#### Sample size

A sample size of 160, with 80 per group, is required for a power of 80%, with a significance of 5%, assuming an effect size of 0.50 and allowing for a 20% dropout rate. The effect size was determined using data from previously published research^14^ compared with a cohort of randomly selected patients under the care of RFL. This method ensured that the power calculation was relevant to a United Kingdom (UK) population.

#### Analysis

Descriptive statistics will be used to report patient demographics. The hypothesis will be tested by comparing the difference between the groups in residual AHI (the primary outcome) at the primary endpoint (6 months) using linear regression adjusting for score at baseline and stratification variables (age as a binary variable and ethnicity) on an intention-to-treat basis. Residual AHI has been chosen as the primary outcome measure as, where interface fit is poor, residual AHI has been shown to be high. Furthermore, it is a measure of treatment effectiveness, which can be used for both CPAP and NIV. The pros and cons of each potential primary outcome measure were discussed with PPI workshop attendees who agreed AHI was a suitable and acceptable primary outcome. AHI will be measured for two nights via a home-based cardiorespiratory sleep study, and the worst (higher AHI) of the two nights will be used. The analyses will be repeated using the 3-month results as a secondary outcome measure.

For secondary outcome measures, differences between groups will be compared using linear regression adjusting for respective scores at baseline and stratification variables. The analyses will be repeated using the results at 3 months.

The interface questionnaire will be analysed using descriptive statistics, bivariate analysis and ordinal regression. Dropout rates between groups will be compared using a χ^2^ test. The analyses will be repeated using the results at 3 months.

#### Statistical software

Data will be collected in a RedCap database. Data will be analysed using Excel, SPSS and R.

### Trial design

#### Screening and recruitment

The principal investigator will screen potential participants from patients referred to the RFL sleep and ventilation service. Those whose initial sleep study results in an AHI≥15 will be considered for screening into the study. Screening data will be collected using the SEAR (screened, eligible, approached, randomised) framework.^17^ Demographic information on patients screened for the trial will include age, gender, ethnicity, screening ID and initials. Inclusion and exclusion criteria information will be collected using the electronic case report form (CRF) (collected via the RedCap Database), which allows the identification of ineligible participants and reasons for ineligibility. The date the trial was discussed and written information was provided to potential participants, as well as reasons for non-approach, will be recorded in the electronic CRF (collected by the RedCap database). Where participants decline to participate in the trial, their reason for refusal and subsequent treatment received will be collected using the electronic CRF (collected via the RedCap Database).

Patients will be identified as potential candidates at several points in the pathway depending on their diagnosis and the clinical pathway. Many patients will have completed a home-based cardiorespiratory sleep study, where patients have already provided permission to contact and are on the academic respiratory medicine permission to contact database, they will be sent the invitation letter and participants’ information sheet via their preferred method of contact. A follow-up phone call will be scheduled with a member of the research team. Where the patient has not already given permission to contact, a clinical appointment will be scheduled to explain their sleep study results and offer them the opportunity to participate in the trial.

The trial will be promoted via a trial website and social media. Posters will be displayed in appropriate clinical areas.

#### Baseline assessments

The following demographic and baseline data will be reported:

Age.Ethnicity.Sex.Primary sleep-disordered breathing diagnosis.Pre-existing relevant medical history.Pre-existing relevant medication.Smoking status.Alcohol consumption.Baseline Epworth Sleepiness Score (ESS).^18^Sleepiness-Wakefulness Inability and Fatigue Test (SWIFT) questionnaire.^19^S3 Non-Invasive Ventilation (S3NIV).^20^Baseline AHI.Baseline body mass index.Baseline respiratory rate.Baseline SpO_2_^.^Baseline Waterlow score.Rockwood Frailty score.

#### Assessment

Measurement of the primary outcome at the primary endpoint—residual AHI at 6 months, will be assessed through a two-night home-based cardiorespiratory sleep study. The minimally clinically important difference for AHI has been proposed as five events/hour,^1^ but this has not been assessed in trials or clinical practice. A residual AHI of ≤7 events/hour has been found to indicate good control of SDB.^21 22^ AHI has been found to have some night-to-night variability in patients with mild and severe OSA,^23^ but this has only been investigated during diagnostics and not in response to PAP therapy. To navigate this issue, patients will undertake a home-based limited cardiorespiratory sleep study at baseline, 3 and 6 months to reassess AHI, with the worst (higher AHI) of the two nights being recorded.

Collecting the following measurements will facilitate the assessment of secondary outcome measures:

Interface leak, measured as average L/min and percentage of intentional leak over 7 days from PAP therapy data downloads at 3 months and 6 months.Residual AHI will be measured using PAP therapy data downloads for further validation of AHI, while others have investigated the reliability of PAP therapy data downloads,^21 22^ the software and devices used in this study have not been tested.Incidence of pressure ulcers measured by the European Pressure Ulcer Advisory Panel score (0 to 4).^24^Compliance with PAP therapy, measured as hours and percentage of days PAP therapy used >4 hours/night over 28 days, measured at 3 months and 6 months in concordance with internationally recognised definitions of compliance.Symptoms measured by the ESS and SWIFT measured at baseline, 3 months and 6 months. The ESS measures daytime sleepiness; the SWIFT measures both sleepiness and fatigue.Comfort as measured by the S3NIV questionnaire and the previously piloted interface questionnaire at baseline, 3 months and 6 months. The S3NIV questionnaire measures respiratory symptoms, sleep quality and PAP therapy-related side effects.

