#### Intervention device

The device will be a 3D-printed customised oronasal mask designed to be used with PAP therapy. The mask will be created using a 3D scanner, which captures a digital impression of the patient’s face; CAD will be used to create a mould, which will then be 3D printed, with the mould then used to make the mask. The part of the mask in contact with the participants’ skin will be silicon-based.

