#### Comparator device

Conventional PAP masks will be used in the usual care group. An expert clinician will make a clinical assessment of the fit and decide on the conventional mask. They will all be full face masks. Depending on procurement and supply chain, a range of full-face masks will be utilised.

The PAP devices used will be CE/UKCA marked devices. A range of devices will be used depending on procurement and supply chain. Where feasible, the same manufacturer will be used throughout the study to ensure consistency in the data collected from the PAP devices.

The devices used in the manufacturing process will include the 3D scanner, Revopoint POP 2 (Revopoint, Hong Kong). A range of 3D printers will be used to ensure the sustainability of the research. This includes stereolithography printers (Form 3, FormLabs, Germany), selective laser sintering printers (Lisa Pro, Sinterit, Poland and Fuse 30+, FormLabs, Germany) and Polyjet printers (Object 260, Stratasys).

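### The leak outcome is tied to intentional leak, so its percentage measure depends on mask vent design as well as on fit

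*Protocol article*

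**What the plan says.** The Secondary research objectives section of the protocol article reads: "To assess the clinical impact of customised interfaces on interface fit (leak), concordance with PAP therapy and symptoms compared with conventional interfaces". Leak stands there as the measure of fit. The Introduction uses leak in the same sense: it says PAP effectiveness depends on fit, and presents interface leak as a cause of poor ventilation and high residual AHI.

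The Assessment section then defines the outcome, taken at 3 and 6 months: "Interface leak, measured as average L/min and percentage of intentional leak over 7 days from PAP therapy data downloads". The article does not mention unintentional leak anywhere.

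The masks differ by arm. For the intervention, "The device will be a 3D-printed customised oronasal mask designed to be used with PAP therapy". For the control, "Depending on procurement and supply chain, a range of full-face masks will be utilised". Neither device section describes a vent.

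The Analysis section compares secondary outcomes between arms by linear regression, adjusting for the baseline score and the stratification variables (age group and ethnicity).

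**The concern.** Intentional leak is the flow released by design through the mask's vent. A poor seal shows as the other component, unintentional leak. The definition therefore names a property of the mask, while the objective asks about the seal between mask and face.

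This matters because mask type is the randomised contrast. Any difference in vent flow between the customised mask and the conventional masks lines up with treatment arm, so randomisation does not remove it. Adjustment cannot remove it either: the customised mask occurs in one arm only, so a term for mask design could not be separated from the treatment effect. The remedy has to be in the outcome definition.

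At stake is the interpretation of one secondary measure. A difference in the percentage could come from vent design, from fit or from both, and fit is part of the mechanism behind the trial's hypothesis.

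**Working it through.** **The plan's own figures.** The article gives no figure for leak. Its sample size of 160 concerns the primary outcome and reproduces: an effect size of 0.50 at two-sided 5% and 80% power needs 64 per group by the t-test, and 64 / 0.8 = 80 per group. Nothing below changes it.

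**Notation.** V is vent flow (intentional leak) and U is seal leak (unintentional), both in L/min. Fit is reflected in U.

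**Readings of the definition.**

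1. *Of intentional leak* governs both terms. The L/min measure is then V, which carries no information on fit.
2. The percentage is the intentional share of total leak: 100 × V / (V + U).
3. The percentage is interface leak relative to intentional leak: 100 × U / V.

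V enters all three. On readings 2 and 3, the L/min measure is interface leak with its type unstated. It could be U (sound) or V + U (contaminated by V).

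**Equal fit, unequal vents.** All flows are assumptions, chosen only to show the dependence. Within each row U is the same in both arms; V is 30 in one arm and 30, 35 or 40 in the other.

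| U (both arms) | Reading 2 at V = 30 / 35 / 40 | Reading 3 at V = 30 / 35 / 40 |
|---|---|---|
| 0 | 100 / 100 / 100% | 0 / 0 / 0% |
| 5 | 85.7 / 87.5 / 88.9% | 16.7 / 14.3 / 12.5% |
| 10 | 75.0 / 77.8 / 80.0% | 33.3 / 28.6 / 25.0% |
| 20 | 60.0 / 63.6 / 66.7% | 66.7 / 57.1 / 50.0% |

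For example, at U = 10: 30 / 40 = 75.0% and 40 / 50 = 80.0%. Total leak over the same range differs by 35 − 30 = 5 or 40 − 30 = 10 L/min, whatever U is. Three things follow:

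- With equal vents there is no false difference.
- With no seal leak at all, the percentages on readings 2 and 3 do not move with V.
- Otherwise the arm with the larger vent looks better on the percentage and worse on total L/min, although fit is the same.

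**Unequal fit, equal vents.** Take V = 30 in both arms and U = 5 against 20. Intentional leak in L/min is 30 against 30, so reading 1 misses the difference. Reading 2 gives 30 / 35 = 85.7% against 30 / 50 = 60.0%, so it does register fit.

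The percentage on readings 2 and 3 is therefore a mixture of fit and vent design. It is not blind to fit.

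**The case against.** The strongest reply is that one word is carrying the whole point. *Intentional* may be a slip for *unintentional*. The outcome is headed interface leak, a term the Introduction uses for the harmful leak that goes with poor fit, so the L/min measure may already be seal leak. Whether L/min is net of vent flow, and what the denominator is, are operational details that a journal article may leave to the full protocol or analysis plan. No vent is described for either mask, so a difference between arms is possible but not shown. Fit also leaves traces in other outcomes, such as pressure ulcers and the comfort questionnaires.

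Much of this stands. A missing denominator alone would be no finding. But the article does state a definition, the definition names the wrong component for its objective, and nothing else in the text corrects it. A slip in an outcome definition still needs correcting.

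A reader might infer more than the document supports:

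- **That leak is a key secondary outcome.** The article sets no hierarchy; leak is only listed first.
- **That the leak results could say nothing about fit.** The L/min measure may be seal leak, and the percentage on readings 2 and 3 responds to fit.
- **That a bias of some L/min is established.** Every flow in the working is assumed, and the true difference between vents could be zero.
- **That variety of PAP devices biases the comparison.** The article does say "A range of devices will be used depending on procurement and supply chain", but it does not say device choice differs by arm, and it adds: "Where feasible, the same manufacturer will be used throughout the study to ensure consistency in the data collected from the PAP devices". Adjustment for manufacturer would be a preference and is not needed here.

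**Conclusion.** The point holds as a mismatch between a stated outcome definition and the objective it serves. The percentage depends on designed vent flow on each reading considered, so it can differ by arm when fit is equal. The L/min measure is sound if it means seal leak and unsound if it means vent flow or total leak; the article does not settle which.

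This rests on two assumptions: that intentional leak has its ordinary technical meaning, which the article does not define, and that vent flow may differ between the customised and conventional masks, which the article neither shows nor excludes. The size is unknown because no vent flows are given.

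The consequence is limited to a secondary measure. Residual AHI at 6 months comes from a home sleep study and does not use the leak measure, so the primary analysis and the sample size are untouched. This is a minor but worthwhile correction.

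**What to change.** Define the secondary outcome as average unintentional leak in L/min over the 7 days, obtained by removing the vent flow of the mask in use. Apply one derivation rule in both arms and state the vent-flow value used for the customised mask. If the downloaded figure is already net of vent flow, say so and say what vent flow was assumed for each mask.

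Either drop the percentage, or express unintentional leak as a percentage of a stated denominator and report it as supportive. A denominator that contains vent flow keeps some dependence on mask design, so the L/min measure should carry the fit objective.

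The cost is a change to one outcome definition plus the vent-flow characteristic of the customised mask, which has to be obtained if it is not already known. No new patient procedure and no manufacturer term in the model are required.
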